## Materials and Methods

2

This is a cross-sectional study funded by the São Paulo Research Foundation (FAPESP, process number 2017-07321-9). The protocol registration of this research is available at ClinicalTrials.gov (NCT03986879). The study procedures will take place from November 2018 until the second semester of 2020.

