### Sample

2.2

The sample will include adults aged 18 years or older from the city of Santo Anastacio, located in the southeastern region of Brazil, who are not injecting any type of medicine to control heart rate. Considering that the approximate population with over 18 years of age in the city of Santo Anastacio is 16000 inhabitants (IBGE), a correlation value of r = 0.23 was adopted to calculate the sample size,^[4]^ with an 80% power and 5% alpha, which determined a minimum sample size of 147 subjects.^[7]^ However, predicting possible refusals to participate in the study and losses of the subjects and data, a further 30% was added to the sample, totaling a minimum of 192 subjects to be evaluated. Conversely, as the present study will consider age, sex, and socioeconomic condition as adjustment variables, more 20 subjects was added for each adjustment variable. Thus, the final sample estimated is 252 individuals to be evaluated. The equation below was used to calculate the sample size. 
[figure not shown]

where n = sample size; Zα / 2 = alpha error value (1.96 [5%]); Zβ = beta error value (0.84 [20%]); r = correlation coefficient (Pearson or Spearman).

For sampling, the city of Santo Anastacio will be divided according to census sectors delimitation. This city has a total of 34 census sectors, of which 23 are in the urban area of the city and will be contemplated in this study. The number of people to be interviewed in each of the census tracts will be calculated based on the number of people residing in these sectors, considering the proportional population of each census sector – Table 1. In order to carry out this procedure, the census tracts will be divided based on a geographic map of the city of Santo Anastacio – Figure 1. The neighborhoods will be registered and numbered, as well as the streets and households. Subsequently, the neighborhoods, streets, and homes will be randomly drawn based on the “random” function of SPSS. Residents of the randomly selected households aged 18 or over will be considered eligible to participate in the study and invited to participate. If the selected individuals decline to participate in the research, a new household will be randomly selected, until complete the minimum sample size required for each census sector. This sample selection design was based on the 1st Design of the National Health Survey sample.^[8]^

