### Data collection

2.3

Initially, the evaluators will visit the census sectors drawn and the households that will be part of the sample. In this first evaluation, a face to face interview will be performed using an electronic questionnaire. The questionnaire contains physical activity domains as well as socio-demographic characteristics. After the participants have completed the questionnaires, an accelerometer will be delivered to the research participant with explanations about its use (5-day period). On a pre-scheduled date, the evaluator responsible for delivering the accelerometer will visit to the residence of the participant and perform the accelerometer recall. At that time, the evaluation of cardiac autonomic modulation through analysis of heart rate variability will be scheduled at a predetermined location, being the participant informed about the previous recommendations for this measure procedure – Figure 2.

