### Statistics analysis

2.8

After verification of normality by Shapiro-Wilks test, the variables characterizing the sample will be expressed as mean and standard deviation or median and interquartile range. The dependent variable will be the cardiac autonomic modulation. Pearson or Spearman correlation will be used to analyze the relationship between cardiac autonomic modulation and physical activity. Linear regression will evaluate the magnitude of the relationship between cardiac autonomic modulation and physical activity, both in the unadjusted model and in models adjusted by age, schooling, ethnicity, and socioeconomic status. Confounding variables will be inserted simultaneously into the model. It should be emphasized that linear regression analysis will be performed stratifying the study participants by sex. This same type of analysis will be performed to verify the possible relationships between the different domains of physical activity (work, leisure, and displacement activity) and cardiac autonomic modulation.

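### The fixed adjustment set omits smoking and diagnosed cardiometabolic disease, and no eligibility limit removes them, so the adjusted slopes can carry residual confounding of a size the protocol does not give

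*Protocol article*

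**What the plan says.** **Design.** The protocol states: "This is a cross-sectional study funded by the São Paulo Research Foundation". Confounding can therefore be handled only by restriction, stratification or adjustment.

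**Restriction (section 2.2 and section 2.6).** "The sample will include adults aged 18 years or older from the city of Santo Anastacio" are eligible, limited to those "who are not injecting any type of medicine to control heart rate". At household level, "Residents of the randomly selected households aged 18 or over will be considered eligible to participate in the study". No upper age limit and no smoking or disease criterion is stated. Section 2.6 adds a recording filter (more than 95% sinus beats) and a 12-hour restriction on alcohol and stimulants before the test, with coffee and tea as the examples; tobacco is not named.

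**Stratification (section 2.8).** "linear regression analysis will be performed stratifying the study participants by sex".

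**Adjustment (section 2.8).** Models are fitted "both in the unadjusted model and in models adjusted by age, schooling, ethnicity, and socioeconomic status", with all confounders entered together. The sample-size paragraph in section 2.2 gives a different list: "as the present study will consider age, sex, and socioeconomic condition as adjustment variables". Neither list contains a behavioural or health factor.

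**Data collection (section 2.3).** "The questionnaire contains physical activity domains as well as socio-demographic characteristics". Sections 2.4 to 2.7 describe accelerometry, the activity questionnaire, HRV and economic class. Smoking and diagnoses are not mentioned.

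**The concern.** Smoking and established cardiometabolic disease are plausible common causes of low activity and low HRV. The Introduction itself treats autonomic modulation as a marker of cardiovascular health, which ties the outcome to disease status. A participant who is inactive because of long-standing diabetes, and has low HRV for the same reason, would enter the model as evidence that inactivity goes with low HRV. If such a factor lowers both variables, the bias is positive, which is the direction the hypotheses at the end of the Introduction favour.

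What is at stake is the use made of the slopes. The Perspectives section wants to identify which intensity and amount of activity relates best to autonomic benefit, and to guide health promotion by intensity and domain. That ranking is weakened if an uncontrolled factor contributes to some slopes.

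This is not a detail left open in a condensed article. Section 2.8 names the covariates and calls them the confounding variables, so following it as written gives a model without smoking.

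**Working it through.** **Step 1. Does any design feature cover these factors?**

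| Means of control | What the protocol has | Smoking | Diabetes, hypertension | Cardiovascular disease |
|---|---|---|---|---|
| Restriction | Heart-rate-medicine criterion; more than 95% sinus beats | No | No | In part |
| Stratification | Sex | No | No | No |
| Adjustment | The four covariates in section 2.8 | No | No | No |

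Control is partial for cardiac disease and absent for the rest, apart from whatever the four covariates happen to share with smoking and illness.

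**Step 2. The plan's own figures.** The planning correlation is r = 0.23, with two-sided alpha 5% and power 80% (section 2.2).

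- n = ((1.960 + 0.842)/atanh(0.23))² + 3 = 146.1, rounded up to 147, as stated.
- 147 × 1.30 = 191.1, rounded up to 192, as stated.
- 192 + 3 × 20 = 252, as stated.

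These reproduce. The point does not depend on them; r = 0.23 is used below only as a reference value.

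**Step 3. Illustration of size.** The protocol gives no prevalence of smoking or disease and no correlations, so the following inputs are assumptions. Let one omitted factor have correlation a with activity and b with HRV, both negative and equal, each being the correlation that remains within sex after the planned covariates. Let the observed r be 0.23 on the same footing. Then

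- spurious part = a × b
- r after adjustment = (0.23 − ab)/√((1 − a²)(1 − b²))

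| a = b (assumed) | ab | r after adjustment | Fall from 0.23 |
|---|---|---|---|
| −0.1 | 0.01 | 0.220/0.990 = 0.222 | 3% |
| −0.2 | 0.04 | 0.190/0.960 = 0.198 | 14% |
| −0.3 | 0.09 | 0.140/0.910 = 0.154 | 33% |

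**Step 4. Two factors.** For two mutually uncorrelated factors of the same strength, the expression becomes (0.23 − 2ab)/(1 − 2a²) when a = b.

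- At −0.1: 0.21/0.98 = 0.214.
- At −0.2: 0.15/0.92 = 0.163.
- At −0.3: 0.05/0.82 = 0.061.

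If smoking and disease are positively correlated with each other, the joint fall is smaller than this, so these values mark the far end of the assumed range.

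**The case against.** **The factors may be collected.** A reader might infer that smoking and disease are not asked and so can never be adjusted for. The protocol does not support that. Section 2.3 summarises the questionnaire in one sentence, and the instrument is not shown. The summary is evidently incomplete: the heart-rate-medicine criterion requires medication use to be ascertained, yet no medication item is listed. What can be said is that these factors are not described as collected. The objection stands on this, but it does not rescue section 2.8, which omits them whether or not they are recorded.

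**Not every illness is admitted.** A reader might also infer that adults with any illness enter. The medicine criterion and the sinus-beat filter will remove some cardiac disease. That stands too, but neither limit reaches smokers or people with diabetes or hypertension.

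**The size is assumed.** Correct. The correlations have no source in the protocol. What matters is what is left after the four planned covariates and stratification by sex, which may already absorb part of the effect. At the low end the change, 0.23 to 0.22, is negligible.

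**The effect on the ranking is not documented.** A reader might go further and conclude that a leisure or vigorous advantage is health status alone, because work and displacement activity are spared. Nothing in the protocol shows this, and illness may also reduce walking, cycling and physical work. Even the worst single-factor case above leaves r = 0.154.

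**Disease may be a consequence of inactivity.** Also right. Routine adjustment could remove part of the association under study, so disease belongs in a sensitivity analysis and not in the main model.

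**The aim is associational, and residual confounding is generic.** The wording is indeed about relationships. But the protocol plans adjusted models and health-promotion guidance, and this gap is specific and cheap to narrow.

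**Conclusion.** The point holds in limited form. The adjustment set in section 2.8 is stated and closed. It contains neither smoking nor diagnosed cardiometabolic disease, and the eligibility limits and the sex stratification do not make up for that. The adjusted slopes can therefore carry avoidable residual confounding, plausibly in the direction of the hypotheses.

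Its size cannot be derived from the protocol. On the assumed correlations of −0.1 to −0.3 with both variables, one omitted factor would account for a fall from 0.23 to between 0.22 and 0.15, which is from almost nothing to about one third of the association. The direction assumes that the factor lowers both activity and HRV. The protocol does not show that the factors went unrecorded, or that some activity domains are affected more than others, and neither is claimed here. The change should be made, but the omission does not invalidate the study.

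**What to change.** 1. Confirm whether the electronic questionnaire records smoking status (current, former, never) and self-reported physician diagnosis of diabetes, hypertension and cardiovascular disease. If it does not, add these items. They can be asked at the interview, the accelerometer recall visit or the HRV session, so participants already interviewed but not yet recorded can still be reached.
2. Add smoking status to the adjusted model in section 2.8.
3. Pre-state one sensitivity analysis that either adds an indicator of diagnosed disease or excludes those diagnosed, and give as the reason that disease may partly result from inactivity.
4. When amending section 2.8, reconcile its covariate list with the different one in section 2.2.

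**Cost.** About four short questions at contacts already planned. Three-level smoking status takes two degrees of freedom in each sex-specific model, and a single disease indicator takes one more in the sensitivity analysis. If the planned 252 split evenly by sex (an assumption), that is set against 252/2 = 126 participants per model. If the items are already recorded, the change is an edit to the analysis section only.

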## Introduction

1

Cardiac autonomic modulation has emerged as an important marker of cardiovascular health, providing early information on impairments in cardiovascular function. Disorders in the balance between the sympathetic and parasympathetic nervous system can cause a series of cardiovascular problems. Koopman et al,^[1]^ in an epidemiological study with about 800 African adults, found that low patterns of cardiac autonomic modulation were associated with higher odds of mortality.

Likewise, physical activity has been shown to improve autonomic function.^[2]^ Indeed, several studies have shown that physically active subjects present better cardiac autonomic modulation than physically inactive peers.^[3–5]^ Rennie et al^[3]^ evaluated the practice of physical activity through a questionnaire in English individuals aged 35 to 55 years-old and observed that those subjects who were classified as practicing more vigorous intensity PA presented better autonomic modulation than those located in the lower quartiles of PA intensity. Kaikkonen et al,^[4]^ in a study with 107 obese adults, observed that higher levels of physical activity assessed by means of a questionnaire were positively associated with the SDNN index in adults in Finland. However, Kang et al,^[5]^ in a study of 131 Korean male workers, observed that physical activity recorded in the study was inversely related to cardiac autonomic modulation.

However, some limitations have been pointed-out in the literature, namely the use of only one instrument (questionnaire or accelerometer) to assess physical activity. When an accelerometer is used, although it is possible to analyze the intensity, it is unlikely that the different domains of physical activity can be analyzed without additional information. In general, the different domains of physical activity are analyzed through questionnaires, namely in the work environment, leisure, and through active transport, for example. Thus, the ideal strategy is to use both types of measures of physical activity, enabling verification of which intensity and domain of physical activity tend to be better related to cardiac autonomic modulation. It is also emphasized that men and women tend to present different cardiac autonomic modulation^[6]^ and, thus, analysis stratified by sex should be considered in this relationship.

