Therefore, in the present project, we will investigate the relationship between the different intensities and domains of physical activity with cardiac autonomic modulation in adults. We hypothesize that subjects who perform physical activity at higher intensities will present better cardiac autonomic modulation. Considering the different domains of physical activity, our hypothesis is that physical activity in leisure has a greater relationship with autonomic cardiac modulation as it is carried-out in the free time period when the individual is more likely to be free from work stress and/or because it is, generally, an activity which the subject enjoys practicing.

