### Domains of physical activity

2.5

Habitual practice of physical activity in different domains will be evaluated by the Baecke et al questionnaire.^[13]^ This instrument evaluates the practice of physical activity in the previous 12 months through 16 questions, considering physical effort at work, the practice of sports activities or systematized exercises in leisure, and leisure activities. In the field of work, questions related to the physical exertion carried out at work include: time spent sitting, standing, and walking in the work environment, carrying weights, whether the evaluated subject perspires a lot at work, and how tired they feel after a day's work. In the leisure domain, the practices of physical activities during leisure are considered, such as exercises in the gym or practicing sports. In these domains, the following will be evaluated; the intensity of the physical exertion of these activities (mild, moderate, vigorous), the number of hours in the week in which these activities are practiced, and how long this physical activity has been practiced (<1 month, 1–3 months, 4–6 months, 7–9 months, > 9 months). In the field of occupational activities, the different physical activities in free time are considered, especially considering active displacement, such as the amount of time that is spent walking to the mall, market, or work; the time spent riding a bicycle is also considered.

At the end, this instrument offers a dimensionless score for each domain and the sum of the score of the 3 assessed domains determines the total amount of physical activity. This instrument has been used in different types of epidemiologic studies.^[14,15]^

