## Perspectives of this study

3

The hypothesis of the study is that different intensities and domains of physical activity will present different relationships with cardiac autonomic modulation. It is envisaged that the findings of the present study will provide better understanding about the best intensity and amount of physical activity related to the benefits in cardiac autonomic modulation. In addition, to determine if there are differences between the different domains of physical activity regarding autonomic cardiac modulation could provide guidance towards strategies of health promotion in adult population, which can be elaborated focusing on intensity and domains of physical activity.

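### The hypotheses compare activity domains and intensities, but the stated analysis estimates each association and names no test of a difference

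*Protocol article*

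**What the plan says.** The comparative aim appears in three places in the protocol article.

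- Introduction, on using both an accelerometer and a questionnaire: "enabling verification of which intensity and domain of physical activity tend to be better related to cardiac autonomic modulation".
- Introduction, on domains: "our hypothesis is that physical activity in leisure has a greater relationship with autonomic cardiac modulation".
- Section 3 (Perspectives of this study), as the study hypothesis: "different intensities and domains of physical activity will present different relationships with cardiac autonomic modulation".

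The Introduction's sentence on intensity is different in kind. It predicts that "subjects who perform physical activity at higher intensities will present better cardiac autonomic modulation".

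The analysis is in section 2.8. First, "Pearson or Spearman correlation will be used to analyze the relationship between cardiac autonomic modulation and physical activity". Then linear regressions follow, unadjusted and in "models adjusted by age, schooling, ethnicity, and socioeconomic status", stratified by sex. For work, leisure and displacement the instruction is: "This same type of analysis will be performed to verify the possible relationships between the different domains of physical activity". The covariate list contains no other domain or intensity, and simultaneous entry is stated for the confounders only.

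The sample size in section 2.2 is for one correlation of 0.23 tested against zero.

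**The concern.** A hypothesis that leisure has the greater relationship is a statement about a difference between associations. The stated correlations and regressions each address a different null, namely that one association is zero. A clear result for leisure and an unclear one for work does not show that the two differ, because both estimates carry sampling error.

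At stake is the claim the study most wants to make. Section 3 hopes to guide health promotion by domain and intensity. Without a stated contrast, nothing in the plan tells the authors when they may say greater or different, or how uncertain that statement is.

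A smaller matter bears on the contrast. Section 2.5 first lists the third questionnaire score as leisure activities, then introduces it with "In the field of occupational activities, the different physical activities in free time are considered, especially considering active displacement", and section 2.8 calls it displacement. A contrast involving leisure needs one fixed label per score.

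**Working it through.** **Inputs from section 2.2:** r = 0.23, two-sided 5% alpha (1.96), 80% power (0.84), minimum 147, then 192, then 252. **Assumptions:** an even split by sex (252 / 2 = 126); a correlation between two exposures of 0 to 0.5; the other domain's correlation with heart rate variability (HRV). The article gives none of these.

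**1. The plan's own figure.** With the Fisher transformation, n = ((1.96 + 0.84) / atanh(0.23))² + 3. Since atanh(0.23) = 0.2342, this is 142.95 + 3 = 145.95, so 146; exact normal quantiles give 146.11, so 147. Then 147 × 1.3 = 191.1, so 192, and 192 + 3 × 20 = 252. The stated figures reproduce.

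Power for that single association is Φ(atanh(0.23) × √(n − 3) − 1.96): 80% at 147, 96% at 252 and 74% at 126. None of this concerns a difference between two associations.

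**2. Comparing significance when there is no difference.** Take two exposures equally related to HRV, each tested at 5%. If the exposures are uncorrelated, the chance that exactly one is significant is about 2p(1 − p), where p is the single-association power. For r = 0.23:

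- n = 126: 2 × 0.738 × 0.262 = 0.387
- n = 252: 2 × 0.959 × 0.041 = 0.079

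Simulation (trivariate normal, 20,000 samples per cell) extends this to correlated exposures. Entries are the share of samples with exactly one significant:

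| Both true r | n | Exposure corr. 0 | 0.3 | 0.5 |
|---|---|---|---|---|
| 0.23 | 126 | 39% | 32% | 27% |
| 0.23 | 252 | 8% | 7% | 6% |
| 0.15 | 126 | 48% | 39% | 32% |
| 0.15 | 252 | 44% | 36% | 30% |

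In every cell a direct test of the difference rejects in about 5% of samples, whether done as a test of two dependent correlations or as a contrast of standardised coefficients in a joint model. Section 2.8 stratifies the regressions by sex, so 126 is the relevant size for them. It does not say that the correlations are stratified, so 252 may apply there.

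**3. Power of the direct comparison.** For two correlations sharing the outcome (Meng-Rosenthal-Rubin), Z = (atanh r₁ − atanh r₂) / SE, with SE = √(2(1 − rₓ)h / (n − 3)). Here rₓ is the correlation between exposures, h = (1 − f·m) / (1 − m), m = (r₁² + r₂²) / 2 and f = min(1, (1 − rₓ) / (2(1 − m))).

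With r₁ = 0.23 and r₂ = 0.10 the numerator is 0.1339.

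- n = 252: SE = 0.0903 (rₓ = 0) or 0.0641 (rₓ = 0.5), so Z = 1.48 or 2.09 and power = 32% or 55%.
- n = 126: SE = 0.1285 or 0.0912, so Z = 1.04 or 1.47 and power = 18% or 31%.

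The same calculation for other values of r₂, with ranges running from rₓ = 0 to 0.5:

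| r₂ | Power at 252 | Power at 126 | N for 80% power |
|---|---|---|---|
| 0 | 74% to 96% | 45% to 73% | 294 to 150 |
| 0.10 | 32% to 55% | 18% to 31% | 893 to 452 |
| 0.15 | 15% to 25% | 9% to 15% | 2322 to 1174 |

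**The case against.** The strongest reply is that this is a condensed article and that contrasts, standardisation and mutual adjustment could sit in a fuller plan that is not shown. That is a fair limit on what can be said about the study as a whole. It does not remove the point: the article states both its hypotheses and its methods, and the methods it states address a different null.

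Several stronger readings are tempting, and the text does not support them.

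- A reader might infer that domains will be ranked by p-values. Section 2.8 contains no such rule and speaks of the magnitude of the relationship. The percentages in the second step apply only if significance were used that way.
- A reader might take one regression per exposure as stated. It is the natural reading of the covariate list, but it is an inference. Even if the domains were entered together, no test of a difference is given.
- A reader might say that both Introduction hypotheses are comparative. The intensity sentence predicts an association, which the planned analysis can address. The comparative reading for intensity comes from section 3 and from the rationale for using both instruments.
- A reader might object that scores, minutes and counts cannot be compared. Correlations are scale-free, the domain scores are all dimensionless, and neither hypothesis sets a questionnaire score against accelerometer time.
- A reader might conclude that the leisure exposure is undefined. Section 2.5 ties the leisure domain to gym exercise and sport, and section 2.8 lists leisure and displacement separately. The labelling is mainly a wording slip.

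The size also depends on the assumptions. At the plan's own r of 0.23 and the full 252, comparing significance misleads in only 6% to 8% of samples.

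**Conclusion.** The point holds in a limited form. The domain hypothesis in the Introduction and the general hypothesis in section 3 are about differences, and section 2.8 as written names no test of a difference.

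If significance were used as a substitute, two equally related exposures would appear to differ in about 27% to 39% of samples per sex when both correlations are 0.23, and in about 32% to 48% when both are 0.15. In the pooled sample the figures are 6% to 8% and 30% to 44%. These rest on 126 per sex, exposure correlations from 0 to 0.5, normal data and simulation error of up to about one percentage point.

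It does not follow that the study cannot inform its question. The estimates needed for a comparison will be available; what is missing from the stated method is the comparison itself.

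**What to change.** In section 2.8, prespecify a direct comparison of leisure with work and of leisure with displacement, by one of two routes:

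- one model containing the three standardised domain scores and the covariates, with contrasts between coefficients; or
- a test of dependent correlations.

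Report each difference with its 95% confidence interval. Do the same for the accelerometer intensities if the section 3 hypothesis is kept for them. Claim a greater or different relationship only from these contrasts. If the authors prefer not to add them, restate the hypotheses as descriptive.

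Use one label for each questionnaire score throughout, with the sport and exercise score as leisure, and remove the word occupational from the free-time and displacement score.

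The cost in work is small, since the data are already planned. Two drawbacks should be stated openly. Power for the contrast is low unless the other domain's correlation is near zero, so an inconclusive interval is likely, above all within each sex. And a jointly adjusted model estimates each domain's independent association, which is not the same quantity as its marginal one; the authors should say which of the two their hypothesis concerns.
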